### Recruitment {15}

Recruitment of primary care practices to participate in the study leverages the professional networks of the study’s leadership and co-investigator teams. Study leadership calls potential practices, screening for interest and eligibility.

To recruit study patient participants, the DARTNet Institute identifies potential eligible patients using electronic medical record data from each practice. The data extract contains information on patient visits, medications, and diagnoses. These data retrospectively span at least 24 months and include dates within 12 months of the study start date. Eligible patients are contacted by mail and/or phone with an invitation to participate in the study.

We cannot sample from the entire practice panel of potentially eligible patients because, in most cases, the practices have many more patients with multiple chronic medical and behavioral health conditions than their BHPs can reasonably support, which would limit our ability to capture the effects of each practice’s case finding and clinical management changes on study outcomes. Nor can we allow each practice to know exactly who the consented patient participants are because the practice may tend to concentrate behavioral health resources on those patients in a way not usual in real-world practices, introducing bias. Therefore, we developed a “Community Panel” for each practice consisting of a random subset of the entire practice’s patient population of active adult patients (group A in Fig. 3). Within the Community Panel, some patients will have the target medical and behavioral conditions and be eligible for to participate in the study (group B). The study subjects (group C) are recruited from group B. Because practice change efforts to integrate behavioral health care usually involve increasing the workload of BHPs, the Community Panel size is proportional to the number of BHPs in the practice, approximately 1000 adults per 1.0 full-time equivalent BHP. The Community Panel allows us to conduct a pragmatic trial within the staffing constraints imposed by real-world conditions.

**Fig. 3 Fig3:**
[figure not shown]
Patient participants identification schematic

All practices receive the names of the patients who comprise their Community Panel during the baseline period of the study, but they are not told which ones are eligible for the study or which consented to participate. Control practices may choose to use the Community Panel in the course of their usual care. Active practices are encouraged to focus their redesign efforts (pertaining to screening, case identification, management, follow-up, etc.) on the patients in the Community Panel.

Approximately 8 participating practices will be purposefully selected for inclusion in a qualitatively-driven collective case study of factors that support or impede successful integration of behavioral health and primary care (research question 3). We will identify tiers of “high change” and “low change” practices, where change is defined as the difference between baseline and midpoint median PIP total scores. Practices will be recruited on a rolling basis as midpoint PIP scores become available. Site selection will be informed by emerging findings from both the qualitative data and successive phases of quantitative data that are slated to continue throughout the project period [53].

To estimate the costs of using the IBH-PC toolkit (research question 4), approximately 8 active practices will be recruited using a combination of purposeful and convenience sampling. Selection will be based on practice type, size, location, and capacity to participate in data collection activities. Recruitment and data collection will begin while practices are actively engaged with the IBH-PC toolkit (these sites need not be those selected for the qualitative analysis of research question 3.) The cost analysis was limited to 8 representative practices, in order to minimize data collection burden and optimize response.

### Assignment of interventions: allocation

#### Sequence generation {16a}

Eligible practices are assigned to the active or control arm using a stratified, randomized, approach, in blocks of 4. Randomization blocks are developed using R [54]. Practices are stratified based on degree of behavioral health integration at baseline (total PIP score < 50th percentile vs. total PIP score > =50th percentile) and geographical area.

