### Sample size {14}

Sample size calculations were adjusted for the cluster randomized design [47]. To achieve a nominal significance level of 0.05 for the main hypothesis that any one or more of the eight PROMIS primary outcomes achieves significance, we will apply the Bonferroni correction [48] requiring *P* < 0.05/8 = 0.00625. All PROMIS domain scales are normalized to a standard deviation of 10 points [35]. We assume that the within-practice correlations of the PROMIS scales are 0.03 (similar to the SF-12 [49]). Although minimally important differences [50] are not fully specified, they range from 2 to 8 points for other instruments in the PROMIS series [51, 52].

Power calculations were conducted prior to study recruitment assuming 75 subjects from 40 practices, giving the study 3000 subjects and 90% power to detect a difference in any of the 8 PROMIS scales of 2.5 points or more. With 45 practices recruited, 43 practices randomized to intervention or control, and 2 practices considered as “Vanguard” the study recruitment meets these power and sample size expectations.

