### Statistical methods

#### Statistical methods for primary and secondary outcomes {20a}

Research question 1: does using the IBH-PC toolkit, a practice-level intervention, affect patient-centered outcomes in adults with multiple chronic medical and behavioral health conditions?

For the primary outcomes, we will use generalized linear mixed (GLM) models [64] of patient health status (PROMIS-29 scales) to perform intention-to-treat analyses [65] as a function of experimental condition (active vs. control) and patient characteristics, with patients clustered within practices. The parameters of interest are the central tendency (mean), statistical significance (*P* values), and 95% confidence intervals (CI) of the adjusted change in PROMIS-29 domain from baseline to follow-up. Each of the 8 outcome domains in the PROMIS-29 will be modeled individually as 8 separate hypotheses with adjustment for multiple comparisons and for clustering within practices.

Patient characteristics will be measured at baseline and will include age, gender, race, ethnicity, marital status, employment, education, and income.

For secondary patient outcomes, including change in other patient-reported measures of health and quality of care, and measures of patient disease control from baseline to follow-up, we will use similar GLM models as above but will not adjust for multiple comparisons.

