#### Research question 2: does using the IBH-PC toolkit affect the degree of practice-level behavioral health care integration in primary care practices?

We will use GLM models of practice integration level (total PIP and PIP domains) to perform intention-to-treat analyses as a function of experimental condition (active vs. control) and practice characteristics. The parameters of interest are the central tendency (median), statistical significance (P values) and 95% CI of the change in total PIP and PIP domains from baseline to follow-up.

Practice characteristics will be measured at baseline and will include ownership type, specialty, training status, non-profit status, size, region, census-tract based variables, primary care medical home (PCMH) status, and % Medicare patients.

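### The primary PROMIS-29 model omits the two randomization stratifiers (baseline PIP and geographical area), so it may be conservative and give up precision, to the extent that the strata predict the outcome

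*Protocol article*

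**What the plan says.** Sequence generation {16a} assigns practices "using a stratified, randomized, approach, in blocks of 4". It states: "Practices are stratified based on degree of behavioral health integration at baseline". This first stratifier is total PIP, split at the 50th percentile, and the second is area: "total PIP score > =50th percentile) and geographical area". The number of areas is not stated.

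Statistical methods {20a}, research question 1, models each of the eight PROMIS-29 domains "as a function of experimental condition (active vs. control) and patient characteristics, with patients clustered within practices". It then names the covariates: "Patient characteristics will be measured at baseline and will include age, gender, race, ethnicity, marital status, employment, education, and income". Neither stratifier is in that list. The secondary patient outcomes use similar models.

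Practice-level covariates appear only under research question 2, where the PIP outcomes are modelled "as a function of experimental condition (active vs. control) and practice characteristics": "Practice characteristics will be measured at baseline and will include ownership type, specialty, training status, non-profit status, size, region", followed by a few others. Elsewhere, geography is a practice subgroup (Subgroup analyses {20b}), and PIP is an exploratory replacement for the arm term (Exploratory analyses).

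**The concern.** Blocking within strata balances the arms on the stratifiers, which takes stratum differences out of the sampling variance of the arm contrast. A model without the strata does not know this. It leaves stratum differences in the practice random effect and reports a standard error that includes them. If the strata are prognostic, the test then runs below its nominal level and the confidence intervals are wider than the design warrants.

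The place where precision could be lost is the practice level. With the article's ICC and about 72 patients per practice, between-practice variance makes up 69% of the variance of a practice mean (shown in the working), and recruiting more patients per practice cannot reduce that part. Practice-level covariates can. The trial's own hypothesis, that integration improves patient outcomes, makes baseline PIP a plausible predictor.

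**Working it through.** **Inputs from the article.** SD 10, ICC 0.03, difference 2.5 points, 40 practices of 75 patients, stated power 90%, and significance level "0.05/8 = 0.00625" with sidedness not stated (Sample size {14}). As recruited: 20 active and 22 control practices, and 3006 patients with baseline surveys (Trial status), so 3006/42 = 71.6 per practice.

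**Assumptions not in the article.** R, the share of between-practice variance explained by the strata; ICC 0.03 and SD 10 applied to change scores; the number of areas. Loss to follow-up is ignored.

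**1. The plan's own power figure.**
- Design effect = 1 + 74 × 0.03 = 3.22; effective n per arm = 1500/3.22 = 465.8.
- SE = 10 × √(2/465.8) = 0.655, so 2.5/0.655 = 3.815.
- Two-sided 0.00625 (z = 2.734): power = Φ(1.081) = 86.0%.
- One-sided 0.00625 (z = 2.498): power = Φ(1.318) = 90.6%.

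The stated 90% is thus reproduced one-sided. Two-sided it would need something more, such as adjustment for baseline score: 89.7% at an assumed baseline correlation of 0.3. This is separate from the present point. Two-sided tests are used below.

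**2. Standard error as recruited.**
- Between-practice variance = 0.03 × 100 = 3; within-practice variance = 97.
- Variance of a practice mean = 3 + 97/71.57 = 4.355; between-practice share = 3/4.355 = 69%.
- SE with strata in the model = √[(3(1 − R) + 97/71.57) × (1/20 + 1/22)].

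| R | SE with strata | SE without strata (0.645) is larger by | Power with strata, normal approximation |
|---|---|---|---|
| 0 | 0.645 | 0% | 87.3% |
| 0.1 | 0.622 | 3.6% | 90.0% |
| 0.2 | 0.599 | 7.7% | 92.5% |
| 0.3 | 0.574 | 12.3% | 94.7% |

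These figures assume perfect balance within strata and charge nothing for degrees of freedom, so they show the best case.

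**3. Simulation with incomplete blocks.** With 42 practices, blocks of 4 and 4 or 8 strata, the model without strata behaved as follows.
- R = 0: average model SE 0.64 against a true SD of the estimate of 0.64–0.65, so no excess.
- R = 0.2: 0.63–0.64 against 0.59–0.60, with type I error about 0.0045 instead of 0.00625.

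**4. Simulation of main effects for PIP stratum and area.** t-tests on practice means, two-sided 0.00625, 2.5 points, R split equally between the two factors, 8000 runs per setting. The Monte Carlo standard error is about √(0.84 × 0.16/8000) = 0.4 percentage points.

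| Areas | R | Power without strata | Power with strata |
|---|---|---|---|
| 2 | 0.1 | 83.9% | 86.0% |
| 2 | 0.2 | 83.7% | 88.7% |
| 2 | 0.3 | 85.6% | 92.1% |
| 7 | 0 | 82.6% | 78.5% |
| 7 | 0.1 | 84.5% | 82.6% |
| 7 | 0.2 | 84.4% | 86.1% |
| 7 | 0.3 | 85.1% | 89.4% |

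Across repeated simulations at R = 0.2 the range was about 84–85% without strata and 86–90% with them. With seven areas and R of 0.1 or less, adjustment lost about 1 to 4 points. One term per stratum cell does worse: with 14 cells and R = 0.2, power fell from 85% to 82%.

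**The case against.** The strongest objection is that the loss is conditional. A reader might infer from the mismatch that the standard errors are simply too large. The article does not support that, because it never says how much of the practice variance the strata explain, and at R = 0 there is no excess at all. The outcome is change from baseline, so stable differences in level between areas or PIP groups cancel, and the strata would have to predict change. This stands, and it is why R = 0 belongs in the range.

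A reader might also infer that adjustment is needed to repair stratum imbalance left by the 20 vs 22 split and the withdrawn practice. Trial status gives arm totals only, so imbalance within strata can be neither shown nor excluded.

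A third tempting step is to fault the PIP models under research question 2 in the same way. Those models already list region, and their outcome is change in PIP from baseline. Whether baseline PIP should also be a covariate there is a choice between analysis of covariance and a change score, which is a different question.

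Finally, this is a condensed article, and an analysis plan that is not shown could add the strata; the covariate list says what is included and does not exclude design factors. That lowers confidence but does not remove the point. The article names its covariates for research question 1, all of them patient variables, and names practice variables where it intends them.

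**Conclusion.** The point holds as one of precision, with a modest and conditional effect. The design stratifies on two practice-level factors, and the stated primary model contains neither. Any resulting error is conservative: intervals too wide and P values too large, never the reverse, so validity is not at risk.

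The reduction in standard error runs from none at R = 0 to 11% at R = 0.3 (0.645 to 0.574). At R = 0.2 the realistic power gain is roughly 2 to 5 points, depending on the number of areas. With many areas and weakly prognostic strata the gain turns into a small loss. All of this rests on an assumed R, on ICC 0.03 holding for change scores, and on an unknown number of areas.

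**What to change.** In Statistical methods {20a}, research question 1, add two main effects to the eight primary PROMIS-29 models and to the secondary patient-outcome models: the PIP randomization stratum (or continuous pre-randomization total PIP) and geographical area. Do not fit one term per stratum cell. State the number of areas, and keep them few or group them by a rule fixed without sight of outcomes by arm.

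Both factors were needed to place each practice in its stratum, so no new data are required. Follow-up collection has ended and data processing is under way, so the wording should be settled before outcomes are compared by arm. The cost is practice-level degrees of freedom: one for PIP and one fewer than the number of areas. With about seven areas that is seven of the 40 left by a two-arm comparison of 42 practices, which is where the 1 to 4 point loss at R of 0.1 or less comes from.

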#### Concealment mechanism {16b}

Randomization cards are a dark color, in order to prevent transparency, and individually sealed in opaque manila envelopes. Randomization envelopes are shuffled within block, numbered sequentially within strata and stored in a locked file cabinet. Potential subversion is guarded against by storing the randomization envelopes in a locked file cabinet and only accessing the envelopes when at least two members of the study team are present.

#### Implementation {16c}

When a practice is deemed eligible and ready to be randomized, a data analyst determines which stratum they belong to and opens the next randomization envelope within that stratum. She writes the practice’s name and date of randomization on the card, and then initials the card before filing it. The site’s randomization status is communicated to the Principal Investigator (PI) who sends an email to the practice and notifies the study Practice Change team.

### Assignment of interventions: blinding

#### Who will be blinded {17a}

Once a study practice has been randomized, their assigned study arm is not blinded. Practices are blinded as to who the patient participants are within their practice.

#### Procedure for unblinding if needed {17b}

Not applicable. This study is an unblinded, practice-level intervention.

### Data collection and management

#### Plans for assessment and collection of outcomes {18a}

The main source of outcomes data and descriptors are the patients and practices themselves. On-line surveys are collected and managed using the Research Electronic Data Capture (REDCap) system, a secure, web-based application designed to support data capture for research studies [55]. We also offer patients the option of completing the forms by telephone with a trained interviewer using a scripted interview, or via paper using a mail-in option. Outcome measures are collected at three timepoints: baseline, midpoint, and follow-up. The baseline period reflects the first 0–12 months of participation after randomization, midpoint is 9–12 months after baseline, and follow-up is 18–21 months after baseline. The Data and Analysis Team reviews all records for potential errors.

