#### Intervention description {11a}

The intervention, the IBH-PC toolkit, is a set of implementation strategies consisting of four components:
An online educational curriculum,A structured, team-based, practice redesign and implementation workbook,Remote QI coaching services for internal QI facilitators, andAn online learning community.

The purpose of the IBH-PC toolkit is to guide and support primary care practices through a practice change process as they work to increase their degree of behavioral health integration through, for example, improvement of screening, case identification, management, or follow-up. Progress through the toolkit and use of its components are expected to be variable among participating practices, taking from 9 to 24 months.

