### Outcomes {12}

#### Research question 1: does using the IBH-PC toolkit, a practice-level intervention, affect patient-centered outcomes in adult patients with multiple chronic medical and behavioral health conditions?

##### Primary outcomes

Change in mean patient Patient-Reported Outcomes Measurement Information System [35] (PROMIS-29) scores from baseline to follow-up for eight domains:
Physical functionAnxietyDepressionFatigueSleep disturbanceSocial functioningPain intensityPain interference

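### Baseline surveys may be taken up to 12 months after randomization in unblinded practices, so the primary change score can subtract part of any active-arm effect; how much cannot be derived from the article

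*Protocol article*

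**What the plan says.** All references are to the protocol article.

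- **Timing of surveys** (Plans for assessment and collection of outcomes {18a}): "The baseline period reflects the first 0–12 months of participation after randomization". The later surveys are counted from that survey; "follow-up is 18–21 months after baseline".
- **Primary outcome** (Outcomes {12}): change in mean PROMIS-29 "scores from baseline to follow-up for eight domains". Statistical methods {20a} names the parameter as the "adjusted change in PROMIS-29 domain from baseline to follow-up".
- **Knowledge of arm** (Who will be blinded {17a}): "Once a study practice has been randomized, their assigned study arm is not blinded". Under Implementation {16c}, the allocation goes to the principal investigator, "who sends an email to the practice and notifies the study Practice Change team".
- **Length of toolkit use** (Intervention description {11a}): "Progress through the toolkit and use of its components are expected to be variable among participating practices, taking from 9 to 24 months".
- **Panel list** (Recruitment {15}, after Fig. 3): "All practices receive the names of the patients who comprise their Community Panel during the baseline period of the study". Confidentiality {27} adds that the list is transferred once patient recruitment is complete, and the consent section {26a} places consent at the end of the baseline surveys.
- **Order of toolkit work** (Practice redesign and implementation workbook): start-up, planning and redesign come before implementation. This sequence is intended but not mandatory.

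**The concern.** A baseline in a change score should be free of treatment. Here it is defined as a survey taken after the practice has been randomized and told its arm, within a window of up to a year, while toolkit use is expected to take 9 to 24 months. If practice-wide work begins soon after randomization, some active-arm patients give their baseline when care has already begun to change. That part of the effect is then subtracted. Control practices have no such loss, so the arm difference shrinks toward zero if the toolkit helps.

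Because follow-up is counted from baseline, it falls between 0 + 18 = 18 and 12 + 21 = 33 months after randomization. One change score therefore pools patients with quite different lengths of exposure. What is at stake is a missed or understated benefit on the eight primary domains.

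**Working it through.** **1. The plan's own power figure.** Inputs from Sample size {14}: 40 practices of 75, SD 10, within-practice correlation 0.03, alpha 0.05/8 = 0.00625, difference 2.5 points.

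- Design effect = 1 + 74 × 0.03 = 3.22. Effective n per arm = 1500/3.22 = 465.8.
- SE = 10 × √(2/465.8) = 0.655.
- Power, one-sided 0.00625: Φ(2.5/0.655 − 2.498) = 90.6%, which matches the stated 90%.
- Power, two-sided 0.00625: Φ(2.5/0.655 − 2.734) = 86.0%. With baseline adjustment and an assumed correlation of 0.3 it is 89.7%.

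The article states neither sidedness nor a baseline correlation, so 90% is taken as given below.

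**2. Share of the effect already in baseline.** The article gives neither the spread of baseline dates nor the start of toolkit exposure. Assumptions: baselines are spread evenly over months 0–12 after randomization, and the effect is zero for a lag of L months and then rises linearly to its full size over R months. The mean share at baseline is

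- (12 − L)² / (24R) when 12 − L ≤ R;
- 1 − (L + R/2)/12 when 12 − L > R.

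| Build-up R | No lag | 6-month lag | 9-month lag |
|---|---|---|---|
| 9 months | 62.5% | 16.7% | 4.2% |
| 12 months | 50% | 12.5% | 3.1% |
| 18 months | 33.3% | 8.3% | 2.1% |
| 24 months | 25% | 6.3% | 1.6% |

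Examples: R = 9, L = 0 gives 1 − 4.5/12 = 62.5%. R = 12, L = 6 gives 36/288 = 12.5%. R = 12, L = 9 gives 9/288 = 3.1%. If toolkit work starts only after baseline, every cell is zero.

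**3. A second effect to keep apart.** With slow build-up, some effect may also arrive after follow-up. For R = 24 and no lag, the mean change captures 69% to 73% of the full effect (follow-up at 18 or 21 months). Even a baseline at month 0 would capture only 18/24 = 75% to 21/24 = 87.5%. Not all of the shortfall in such cases is due to the late baseline.

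**4. What a given loss would do to power.** Calibrated to the stated 90%, with a share f of the 2.5 points subtracted: power = Φ((1 − f) × (2.734 + 1.282) − 2.734).

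| f | Observed difference | Power |
|---|---|---|
| 0 | 2.5 | 90% |
| 0.031 | 2.42 | 88% |
| 0.125 | 2.19 | 78% |
| 0.25 | 1.875 | 61% |
| 0.50 | 1.25 | 23% |
| 0.625 | 0.94 | 11% |

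On the plain two-sided inputs (86% at f = 0), the figures for f = 0.25 and 0.50 are 55% and 20%.

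**The case against.** Much of the defence stands.

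- **The decisive fact may be in a figure.** The article refers to Fig. 2 for timeframes. The figure is not shown, and it could place toolkit start after baseline. This stands: the loss may be zero.
- **The panel list is held back.** Patients consent on completing the baseline surveys, and the list is sent once recruitment is complete. Redesign work aimed at panel patients should therefore follow their baselines. This stands for panel-targeted changes. It does not cover practice-wide changes from the curriculum, coaching and workbook, which need no list. Not knowing who participates does not shield patients from such changes either.
- **Patients would notice late.** The workbook puts implementation last, so a lag is the natural reading. This stands, and it is why the lagged columns belong in the range. The sequence is optional, however, so a lag is not assured.
- **Time of measurement is a covariate.** The missing-data section {20c} describes models with time as an explicit covariate. Since the visits are anchored to baseline, this does not by itself capture exposure since randomization.
- **The bias cannot create a benefit.** It runs toward no effect if the toolkit helps. This is true and limits the harm to a missed or understated effect.

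A reader might infer that practices complete the toolkit by month 9 and are surveyed afterwards, or that the change score loses a quarter to more than half of the effect. The documents support neither. The 9 months is an expected duration of use, not a time since randomization, and losses that large need exposure and benefit from month 0 with evenly spread baselines.

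**Conclusion.** The point holds as a defect in how baseline is fixed, not as a demonstrated loss. As written, the plan permits a baseline up to 12 months after an unblinded randomization, sets no visible hold on practice-wide toolkit work, and takes change from that baseline as the primary parameter. Effect present at baseline is then removed in the active arm only.

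The amount cannot be derived. Under even baseline dates, build-up of 9 to 24 months and lag of 0 to 9 months, it ranges from a few percent (3.1% for a 12-month build-up after a 9-month lag, and 1.6% at the slowest build-up) to about 62%. It is zero if exposure follows baseline. The power figures in the working illustrate these assumptions and do not estimate the trial's actual power. The stated 90% is not challenged here.

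**What to change.** Keep all randomized practices and enrolled patients in the analysis, and keep the planned change analysis. Before outcomes are analysed:

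1. **State when toolkit exposure began** relative to the baseline surveys. If it always followed them, say so; the concern then falls away.
2. **Pre-specify a companion analysis** that does not subtract possibly exposed baselines. This can be a longitudinal model on time since the practice's randomization, in which surveys taken after toolkit start are post-exposure records with arm-specific means. Alternatively, compare follow-up scores by arm, adjusted for the planned patient characteristics.
3. **Add a sensitivity analysis** limited to early baselines, with the same months-since-randomization cut-off in both arms.
4. **Report months from randomization to baseline** by arm.

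Each practice's randomization date is recorded on its card (Implementation {16c}). The article does not say that toolkit start dates are held. Where they are missing, months since randomization must serve.

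The cost is analysis wording and somewhat wider intervals where the baseline is not used. The early-baseline subset should stay a sensitivity analysis, because it selects patients on timing that arises after randomization in unblinded practices. Accepting only surveys taken on or before randomization is not workable: with baseline defined as after randomization, almost none might remain.
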